### Document conservation and summary

Documents, such as the ICFs, signatures of participants and others are clearly requested to be retained by researchers after the study according to Good Clinical Practice (GCP). Researchers should retain the clinical trial material for at least 5 years.

### Trial management

#### Data management

We will use RRMS (http://www.medresman.org/login.aspx) to manage the trial data. RRMS can automatically generate an electronic Case Report Form (eCRF) for each. Access to the eCRF password will be protected by administrator of the study on RRMS. All data will be entered into RRMS and can be checked publicly. The consistency of the data will be independently entered by two personnel (double data entry). Once the data have been input into RRMS, any changes can be tracked by RRMS to ensure the accuracy of the data. All the data will be checked by three people in the following order: quality controller of the study, the principal investigator (PI) of the study, and the staff of the GCP office of the Fifth Affiliated Hospital of Guangzhou Medical University (range checks for data values).

#### Management of acupuncture treatment

In principle, the acupuncture treatment will be carried out by the same professional Chinese doctor. If this doctor not available, another well-trained professional Chinese doctor will carry out the acupuncture instead and should sign his name on the eCRF. Sterile acupuncture needles made by Huan Qiu in Jiangsu Province of China will be used; specification: 0.3 × 25 mm; 0.3 × 40 mm.

#### Management of herbal medicine

Participants will receive the herbal medicine from the TCM pharmacy in the Fifth Affiliated Hospital of Guangzhou Medical University with a prescription from the researchers and will be taught how to make the decoction.

#### Management of protocols

Change in protocol: all changes in protocol will be documented, and any modifications of the protocol, including informed consent, must obtain the approval of the Ethics CommitteeCase Report Form (CRF) tracking: all signed ICFs must be submitted before the participants are included. Any questions or comments about CRFs must be submitted directly to the PI

### Researcher’s responsibility

Researchers must understand and strictly adhere to the details of the protocol. They should have enough time to complete the study as scheduled and are responsible for explaining the study process to participants and obtaining informed consent. Participants who experience AEs should be treated appropriately, and related data should be accurately and thoroughly recorded.

### Quality control

#### Quality control of the laboratory

The GCP office of the Fifth Affiliated Hospital of Guangzhou Medical University has established a uniform standard operating procedures (SOPs) and quality control procedureInterventions will be conducted by trained researchers in the hospital, and the hospital can provide suitable medical equipment and emergency facilities

#### Request for researchers

Researchers in this trial must possess the qualifications and ability needed to conduct the research and will not be continually changed.

#### Measures for compliance of participants

Researchers should verify that the participants have received the herbal medicine in time and should explain how to make the correct decoction. Participants in both the treatment group and lifestyle group will be asked to visit the researchers every 8 days to receive acupuncture treatment and new herbal medicine or to receive only the examination by diagnostic methods. The lifestyle diary will be checked by researchers every 4 weeks. Therefore, participant compliance can be examined by the researchers.

#### Monitoring and inspection

Participant data during treatment and follow-up should be entered into RRMS within 2 weeks of being collected. All the data will be checked by three people in the following order: quality controller of the study, the PI of the study, the staff of the GCP office of the Fifth Affiliated Hospital of Guangzhou Medical University (range checks for data values). We will invite the staff of RRMS to inspect the data when the study is finished. The Standard Protocol Items: Recommendations for Interventional Trials (SPIRIT) 2013 Checklist is available in Additional file 3.

#### Bias control

Any other Western or TCM medication that the participants take during the observation period will be recorded, and drugs that have antidiabetic therapeutic effects will be prohibited. The researchers will pay close attention to the study interventions to prevent the occurrence of bias.

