### Progress of prediabetes

It is currently generally accepted that the most effective treatment for prediabetes is lifestyle intervention. The main risk factors for type-2 diabetes include genetics, ethnicity, age, overweight or obesity, unhealthy diet, insufficient physical activity, and smoking. Other than genetics, ethnicity and age, all of the other factors can be modified through behavioural and environmental changes. A 20-year follow-up study in China, *Da Qing* (China *Da Qing* Diabetes Prevention Study (CDQDPS)) [9], showed that compared with control participants who did not receive an intervention, IGT patients who underwent an active lifestyle intervention for 6 years had a 43% lower incidence of diabetes mellitus and a 13% lower 20-year cumulative incidence over the 20-year period. According to the well-known American Diabetes Prevention Program (DPP) [10], which included 3234 fasting plasma glucose (FPG) patients and had an average follow-up of 2.8 years, the incidence of diabetes mellitus development each year in participants in the placebo, metformin and lifestyle groups was 11.0%, 7.8%, and 4.8%, respectively. The DPP also showed that a lifestyle intervention was more effective than metformin. A systematic review and meta-analysis of different intervention strategies for preventing type-2 diabetes [11] revealed that several pharmacological interventions (for example, antidiabetic drugs, cardiovascular drugs, and lipid-affecting drugs) also prevented or delayed type-2 diabetes mellitus; however, in the majority of studies, pharmacological interventions were not as effective as changing diet and physical activity, and the effects dissipated after the medication was discontinued. The Global Report on Diabetes, published by the World Health Organization (WHO) in 2016 [3], suggested that diet and physical activity interventions are more effective than medication for preventing diabetes mellitus. As there is a lack of sufficient evidence showing that pharmacological interventions have long-term efficacy and health economic benefits for patient with prediabetes, the latest guidelines for the intervention and treatment of type-2 diabetes released in 2013 by the Chinese Diabetes Society [12] did not recommend using pharmacological interventions to prevent diabetes mellitus. Therefore, it is accepted worldwide that the most effective method of preventing diabetes mellitus is lifestyle intervention based on health education.

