### Outcome measures

#### Endpoint events

Occurrence of type-2 diabetes (according to the 2016 ADA diagnostic criteria for prediabetes [40, 41])Blood glucose change to normal (FPG <5.6 mmol/L, OGTT 2-hPG <7.8 mmol/L, and HbA_1c_ <5.7%)

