#### Primary outcomes

Fasting plasma glucose (FPG): fasting is defined as no caloric intake for at least 8 h2-h plasma glucose (2-hPG) level after 75-g oral glucose tolerance test (OGTT): the test should be performed as described by the WHO, using a glucose load containing the equivalent of 75 g anhydrous glucose dissolved in waterGlycosylated hemoglobin (HbA_1c_)

All the primary outcomes will be tested on visit 1 (within 1 week before the study), visit 25 (after 24 weeks), and visit 26 (after 48 weeks).

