#### Additional indicators

Body Mass Index (BMI): BMI = weight (kg)/square of height (m^2^). The weight and height of participants will be measured by the same equipment in the Medical Examination Centre of the Fifth Affiliated Hospital of Guangzhou Medical UniversityIncidence of type-2 diabetes mellitus

Calculated using the following formula:$$ \mathrm{Incidence}\ \mathrm{of}\ \mathrm{diabetes}\ \mathrm{mellitus} = \mathrm{Cases}\ \mathrm{of}\ \mathrm{diabetes}\ \mathrm{mellitus}/\mathrm{Total}\ \mathrm{cases}\ \mathrm{of}\ \mathrm{each}\ \mathrm{group} \times 100\% $$
Reversion rates of FBG, 2-hPG after 75-g OGTT, and HbA_1c_ after 48 weeks of follow-up;

Calculated using the following formula:$$ \mathrm{Reversion}\ \mathrm{rate} = \mathrm{Cases}\ \mathrm{o}\mathrm{f}\ \mathrm{blood}\ \mathrm{glucose}\ \mathrm{t}\mathrm{hat}\ \mathrm{have}\ \mathrm{returned}\ \mathrm{t}\mathrm{o}\ \mathrm{normal}/\mathrm{cases}\ \mathrm{o}\mathrm{f}\ \mathrm{each}\ \mathrm{group} \times 100\% $$

BMI will be tested on visit 1 (within 1 week before the study), visit 25 (after 24 weeks), and visit 26 (after 48 weeks).

Incidence of type-2 diabetes mellitus, reversion rates of FBG, 2-hPG after 75-g OGTT, and HbA_1c_ will be calculated only on visit 26 (after 48 weeks).

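### Antidiabetic drugs are banned with no rescue rule for diabetes found at visit 25, and the reversion definition does not exclude participants on such drugs (minor)

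*Protocol article*

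**What the plan says.** All references are to the protocol article.

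- *Bias control*: other "medication that the participants take during the observation period will be recorded", and "drugs that have antidiabetic therapeutic effects will be prohibited". No exception is given. The observation period is not a term used under *Data collection points*, which names only a screening period, a 24-week intervention period and a follow-up of 48 weeks after the intervention.
- *Endpoint events*: the two events are "Occurrence of type-2 diabetes" and "Blood glucose change to normal (FPG <5.6 mmol/L, OGTT 2-hPG <7.8 mmol/L", with HbA1c below 5.7% as the third condition. Nothing requires the participant to be off antidiabetic drugs or free of an earlier diabetes diagnosis.
- *Primary outcomes*: "All the primary outcomes will be tested on visit 1 (within 1 week before the study), visit 25 (after 24 weeks"), and again at visit 26.
- *Additional indicators*: diabetes incidence and the "Reversion rates of FBG, 2-hPG after 75-g OGTT" and HbA1c "will be calculated only on visit 26 (after 48 weeks").
- *Rejection*, *Suspension* and *Dropout criteria*: none names the onset of diabetes or the start of an antidiabetic drug.

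**The concern.** The trial expects some participants to become diabetic and has a scheduled test at visit 25 that can show it. The article does not say what happens next to such a participant, either in care or in endpoint classification.

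Two things are at stake, and they are alternatives. While the ban is in force, a participant diagnosed by the trial is barred from standard drug treatment. Once it has lapsed or been broken, a treated participant can reach visit 26 with all three values below the limits. The definition as written then scores that participant as reverted, although the unfavourable endpoint event has already occurred. No rule says which status prevails.

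**Working it through.** The article states no figure on this point, so there is nothing to reproduce. The check has two parts.

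**1. The rules under each reading of the ban**

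| Reading | Drug treatment after visit 25 | Consequence |
|---|---|---|
| Ban covers follow-up and is obeyed | None | Conflict with standard care; no drug-masked reversion |
| Ban covers follow-up and is breached | Yes | Drug-masked reversion possible |
| Ban ends with the intervention | Permitted | No conflict with care; drug-masked reversion possible |

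No reading is free of a problem. If visit 26 is missing, last observation carried forward (*Analysis of datasets*) brings the diabetic visit-25 values forward, so no false reversion arises.

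**2. Size**

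Inputs from the article:
- 40 participants per arm (*Sample size*).
- Lower rate: 4.8% per year, from the trial whose yearly incidence in the "placebo, metformin and lifestyle groups was 11.0%, 7.8%, and 4.8%, respectively" (*Progress of prediabetes*). The lifestyle figure is the closest match because both arms receive lifestyle intervention (*Groups*).
- Upper rate: 24.3% per 2 years, in people with impaired glucose tolerance only (*Background*).

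Assumptions: constant hazard; hazard halved in the treatment arm where stated; a masked share q of 10% to 50%. A masked case is a week-24 case who is treated, attends visit 26 and has normal values there. The documents give no basis for q.

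*Diabetic by week 24.* With t = 168/365.25 = 0.460 years:
- Lower: p = 1 − 0.952^0.460 = 2.237%; 40p = 0.9.
- Upper: p = 1 − (1 − 0.243)^(0.460/2) = 6.202%; 40p = 2.5.
- With the hazard halved, p is 1.125% and 3.151%.

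*At least one diabetic among 80*, 1 − (1 − p)^80: 84% to 99%. With the hazard halved in one arm: 74% to 98%.

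*At least one masked case among 80*, 1 − (1 − pq)^80, same hazard in both arms:
- Lower rate: 16% (q = 10%) to 59% (q = 50%).
- Upper rate: 39% to 92%.

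*Expected false reversions per 40*, 40pq, same hazard in both arms:
- Smallest: 40 × 0.02237 × 0.10 = 0.09, or 0.2 points.
- Largest: 40 × 0.06202 × 0.50 = 1.24, or 3.1 points.
- One participant is 1/40 = 2.5 points.

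*Shrinkage of the between-arm difference with the hazard halved*, 100 × q × (p_control − p_treatment):
- Smallest: 0.10 × (2.237 − 1.125) = 0.11 points.
- Largest: 0.50 × (6.202 − 3.151) = 1.53 points.

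*Yardstick.* The standard error of a difference between two proportions with 40 per arm is √(2 × 0.3 × 0.7/40) = 10.2 points when both are 30%, and √(2 × 0.5 × 0.5/40) = 11.2 points when both are 50%. The largest shrinkage is about 1.53/10.2 = 0.15 of a standard error.

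**The case against.** **The ban does not cause the misclassification.** A reader might infer that prohibiting the drugs leads to drug-treated diabetics being scored as normal. The text does not support that: an obeyed ban prevents drug-masked reversion. This stands, which is why the two problems are put as alternatives.

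**Other clauses give a way out.** A reader might infer that a diagnosed participant has no route to treatment. That goes too far. *Suspension criteria* allow a participant to be stopped for complications, for unwillingness to continue or for a significant deviation. *Dropout criteria* and *Researcher's responsibility* require appropriate treatment of adverse events. These clauses ease the conflict but do not remove it: they are discretionary and none names diabetes. *Dropout criteria* also ask that participants who leave complete the examinations where possible and stay in the analysis, so on-drug visit-26 values can still enter.

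**Incidence is probably safe.** A reader might infer that cases found at visit 25 are lost because incidence is calculated at visit 26. The natural reading of an occurrence is cumulative, with visit 26 only the time of calculation. A sentence saying so is useful, but this is not a demonstrated error.

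**The full protocol or analysis plan may settle the classification.** Medication is recorded, so treated participants can be identified, and unshown documents may deal with them. That limits the weight of the point. The article nevertheless states both the ban and the laboratory-only definition, and a rule allowing rescue treatment belongs in the protocol rather than in an analysis plan.

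**The effect is small.** This also stands. The bias is conservative if the intervention works, because more such cases then fall in the control arm. It is a fraction of a standard error, in a study described as a pilot.

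**Conclusion.** The point holds as a minor one. The ban has no rescue rule and an undefined duration, and the reversion definition ignores drug treatment and earlier diagnosis. Whichever way the duration is read, either participant care or endpoint classification is left unsound.

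The situation is likely to arise: the chance of at least one diabetic case by week 24 is 84% to 99% with the same hazard in both arms. That must not be read as the chance of a misclassification, which is 16% to 59% at the closest rate and rests on the assumed masked share. The expected shrinkage of the reversion difference, about 0.1 to 1.5 points, depends on a constant hazard, a halved hazard in one arm and that same assumed share. Reversion is an endpoint event compared by chi-square and is not one of the three primary outcomes. The case for a change rests on participant care and a coherent endpoint, not on large bias.

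**What to change.** - In *Bias control*, define the observation period, end the prohibition once diabetes is confirmed, and allow standard treatment from then on.
- In *Endpoint events* and *Additional indicators*, class as not reverted anyone diagnosed with diabetes at visit 25 or 26, or taking an antidiabetic drug.
- In the same sections, state that diabetes is counted cumulatively from first diagnosis.
- In *Analysis of datasets*, state that these participants remain in the full analysis set.

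The cost is a few sentences of amendment. No new data are needed, because all three glycaemic measures are already taken at visit 25 and other medication is already recorded. *Trial status* says that the trial had not started when the manuscript was submitted. The downside is that some visit-26 glucose values will reflect rescue treatment.

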### Informed Consent Form (ICF)

The ICF has been reviewed and approved by the Ethics Committee before initiation of the study. Researchers should inform the participants of the relevant information orally and in writing using understandable language. The ICF must be signed and dated by the participants or their representatives. Before signing the ICF, the participants and representatives should have adequate time to read it. Signed ICFs should be properly retained by both researchers and participants.

### Security

Researchers should carefully maintain participants’ personal information. Participant data in the CRF and RRMS can only be accessed by related researchers and administrators.

## Discussion

We are expecting to discover that, compared with lifestyle interventions, the comprehensive treatments of TCM can be more helpful for preventing prediabetes eventually developing in to diabetes mellitus. And we are also wondering whether TCM methods would cause the side effects of hepatic and renal function impairment. In this trial, we emphasize the importance of individualized treatment for participants with prediabetes. We have made the following adjustments which are different from ordinary protocols of TCM studies in order to match the goal of both individualized and scientific:For demonstrating the precise hypoglycaemic effects of TCM, objective laboratory examinations including FPG, 2-hPG level after OGTT, and HbA_1c_ will provide the primary outcomesFor individual treatment, the changes in participants’ symptoms will be recorded carefully according to four diagnostic methods of TCM including inspection, listening and smelling, inquiry, and pulse-taking and palpation, and will be considered as the basis for adjusting the components and doses of the formula, rather than AEsFor authenticity, we will use RRMS (http://www.medresman.org/login.aspx) to manage the trial data. The changes in participants’ symptoms will be timely entered into RRMS before their next coming and can be checked publicly by a shared password

### Trial status

The trial has been prospectively registered on Chinese Clinical Trial Registry (http://www.chictr.org.cn/showproj.aspx?proj=14986), and has not yet started at the time of manuscript submission.

## Abbreviations

2-hPG: 2-h plasma glucose
ADA: American Diabetes Association
AE: Adverse event
ALT: Alanine aminotransferase
AST: Aspartate aminotransferase
BMI: Body Mass Index
BUN: Blood urea nitrogen
CDQDPS: China *Da Qing* Diabetes Prevention Study
CFDA: China Food and Drug Administration
Cr: Creatinine
CRF: Case Report Form
DPP: Diabetes Prevention Program
eCRF: electronic Case Report Form
FAS: Full analysis set
FPG: Fasting plasma glucose
GCP: Good Clinical Practice
HbA_1c_: Glycosylated hemoglobin A_1c_
ICF: Informed Consent Form
IFG: Impaired fasting glucose
IGT: Impaired glucose tolerance
ITT: Intention-to-treat
LOCF: Last observation carried forward
NPY: Neuropeptide Y
OGTT: Oral glucose tolerance test
PI: Principal investigator
PPS: Per-protocol set
RCT: Randomized controlled clinical
RRMS: ResMan Research Manager
SAE: Serious adverse event
SOPs: Standard operating procedures
SS: Safety set
TCM: Traditional Chinese medicine
WHO: World Health Organization
